## Abstract

**Background:**

In the absence of treatment options, the WHO emphasizes the identification of effective prevention strategies as a key element to counteract the dementia epidemic. Regarding the complex nature of dementia, trials simultaneously targeting multiple risk factors should be particularly effective for prevention. So far, however, only few such multi-component trials have been launched, but yielding promising results. In Germany, comparable initiatives are lacking, and translation of these complex interventions into routine care was not yet done. Therefore, *AgeWell.de* will be conducted as the first multi-component prevention trial in Germany which is closely linked to the primary care setting.

**Methods:**

*AgeWell.de* will be designed as a multi-centric, cluster-randomized controlled multi-component prevention trial. Participants will be older community-dwelling general practitioner (GP) patients (60–77 years; *n* = 1,152) with increased dementia risk according to CAIDE (Cardiovascular Risk Factors, Aging, and Incidence of Dementia) Dementia Risk Score. Recruitment will take place at 5 study sites across Germany. GP practices will be randomized to either intervention A (advanced) or B (basic). GPs will be blinded to their respective group assignment, as will be the statistician conducting the randomization. The multi-component intervention (A) includes nutritional counseling, physical activity, cognitive training, optimization of medication, management of vascular risk factors, social activity, and, if necessary, further specific interventions targeting grief and depression. Intervention B includes general health advice on the intervention components and GP treatment as usual. We hypothesize that over the 2-year follow-up period the intervention group A will benefit significantly from the intervention program in terms of preserved cognitive function/delayed cognitive decline (primary outcome), and other relevant (secondary) outcomes (e.g. quality of life, social activities, depressive symptomatology, cost-effectiveness).

**Discussion:**

*AgeWell.de* will be the first multi-component trial targeting risk of cognitive decline in older adults in Germany. Compared to previous trials, *AgeWell.de* covers an even broader set of interventions suggested to be beneficial for the intended outcomes. The findings will add substantial knowledge on modifiable lifestyle factors to prevent or delay cognitive decline.

**Trial registration:**

German Clinical Trials Register (reference number: DRKS00013555).

## Background

### Relevance

Dementia is not only burdensome for the individuals affected and their relatives, it is also a major public health concern [1]. A substantial increase in the absolute number of people affected is to be expected due to dramatic demographic changes [1, 2]. So far, most types of dementia, particularly Alzheimer’s dementia (AD) as the most common type (60–70% of cases; [3]), cannot be cured. Therefore, the identification of effective strategies for prevention has been emphasized as a key element to counteract the dementia epidemic [4, 5].

Numerous vascular and lifestyle factors have been linked to dementia and AD [6, 7], suggesting that 35% of current dementia cases could be attributed to nine modifiable risk factors (midlife hypertension and obesity, diabetes mellitus, depression, physical inactivity, smoking, low educational attainment, hearing loss, and social isolation [8–11]. Similar results were found for Germany, suggesting a tremendous potential for prevention [10]. Indeed, recent studies indicated trends towards lower dementia incidence in Western high-income countries, likely being the result of improvements in such modifiable lifestyle factors [12]. Further modifiable risk factors may include the use of anticholinergic drugs [13] and atrial fibrillation [14]. Previous randomized controlled trials (RCTs) on interventions aiming at preventing cognitive decline, however, mainly focused on the management of single such risk factors [7]. Regarding the complex nature of dementia as well as the concurrence and interaction of the underlying risk factors, RCTs simultaneously targeting multiple risk factors should be more effective [7]. Large international multi-component trials [15–17] yielded very promising results in this regard.

The *Finnish Geriatric Intervention Study to Prevent Cognitive Impairment and Disability* (FINGER) was the first large RCT providing evidence that a multi-component intervention can be effective in improving or maintaining cognitive functioning in older individuals [5, 16]. Individuals aged 60–77 years (*n* = 1,200) with an increased dementia risk were randomly assigned to receive either a 2-year multi-component intervention (nutritional counseling, physical activity enhancement, cognitive training, vascular risk monitoring) or regular health advice (control group). The primary outcome was change in cognition as measured through a comprehensive neuropsychological test battery (NTB) [16]. During the 2-year follow-up period, cognition improved significantly in the intervention group compared to the control group [5].

In Germany, comparable initiatives have been lacking so far. Thus, the *AgeWell.de* study is designed to first-time investigate prevention potential for cognitive decline through a multi-component intervention, with a focus on modifiable risk factors such as, for example, lifestyle interventions, in older primary care patients in Germany.

### Objectives

The *primary objective* of *AgeWell.de* is to evaluate the effectiveness of a multi-component intervention in preventing or delaying cognitive decline in older adults at increased risk for dementia, specifically tailored to the German health care context. To do so, a pragmatic multi-centric, cluster-randomized controlled prevention trial will be conducted in primary care. The *secondary objective* is to assess effects of the multi-component intervention regarding (i) mortality, (ii) nursing home placement, (iii) functioning in everyday activities, (iv) quality of life, (v) depressive symptoms, (vi) social inclusion, and (vii) the cost-effectiveness of the intervention. A detailed overview of the study aims and associated hypotheses is provided in Fig. 1.

**Fig. 1 Fig1:**
[figure not shown]
Study aims and hypotheses of AgeWell.de

On the one hand, our study will be guided by the FINGER trial by including the components nutritional counseling, physical activity enhancement, cognitive training, and vascular risk monitoring in the 2-year intervention program. On the other hand, we aim to additionally include components of social lifestyle and recommendations on medication overuse and underuse. Encouraging participants to be socially active should also be a beneficial component of the intervention as even in old age an active lifestyle is protective against dementia [6, 18–20]. Likewise, we will provide specific recommendations on the medications of the study participants to their respective GP, if needed. German health claims data suggested that 22–25% of individuals aged 64 years and older receive at least one prescription of a potentially inappropriate medication (PIM) drug within one year [21, 22]. Primary data from a sample of community-dwelling people with dementia indicate that 22% receive at least one PIM with the highest prevalence being antidepressants, benzodiazepines and analgetics [23]. PIM constitutes a major public health concern especially in older age leading, for example, to an increased risk of adverse drug reactions, hospitalization, and mortality [24, 25]. Moreover, PIM is of particular importance as studies strongly suggest that specific drugs (e.g. with anticholinergic properties) can also increase the risk for dementia [13, 26, 27]. On the other hand, medication underuse can modify cardiovascular and other risks [28] and thus outcomes relevant for dementia development.

Finally, we will address further known risk factors for dementia by providing specific interventions in case of bereavement, grief, and depressive symptoms [29, 30], if necessary. The broad range of outcomes will additionally enable the estimation of total benefit and cost-effectiveness of the intervention suggested to be more beneficial for the intended outcomes. The study protocol describes the rationale and the study design of the AgeWell.de trial in adherence to the SPIRIT 2013 statement (Standard Protocol Items: Recommendations for Interventional Trials; [31]).

## Methods

### Study design

To evaluate the effectiveness of a multi-component intervention in preventing or delaying cognitive decline in older adults at risk, a multi-centric cluster-randomized controlled trial with primary care patients will be conducted (Fig. 2).

**Fig. 2 Fig2:**
[figure not shown]
AgeWell.de study design

### Inclusion and exclusion criteria

To target individuals at risk for dementia and suitable for the preventive intervention program, we will include community-dwelling GP patients who are 60–77 years old and have an increased CAIDE Dementia Risk Score (Cardiovascular Risk Factors, Aging, and Incidence of Dementia; [16, 32]). We will use a CAIDE Dementia Risk Score ≥ 9 for inclusion. The risk score predicted dementia risk with a sensitivity of 0.77 and a specificity of 0.63, when a cut-off ≥9 was applied [32]. CAIDE is based on information that is easy to assess (age, education, gender, blood pressure, body mass index, total cholesterol, and physical activity). Therefore, case finding of eligible participants for *AgeWell.de* can be easily conducted in the GP practices. Moreover, the procedure could be transferred into daily care later on.

Exclusion criteria are conditions affecting safe engagement in the intervention (malignant disease/fatal illness, severe clinical depression, symptomatic cardiovascular disease, revascularization within the previous year) as judged by the GP; severe loss of vision, hearing, or communicative ability/insufficient ability to speak and read German; severe mobility impairment; concurrent participation in another intervention trial, and previously diagnosed dementia or dementia suspected by the GP.

### Interventions

During the 2-year follow-up period, participants of intervention group A (advanced) will receive a systematic comprehensive multi-component intervention program (Table 1). All intervention components will be delivered face-to-face by the study nurses during a visit at the participants’ homes. The intervention will includeadvice on healthy nutrition, based on the guidelines of the German Nutrition Society (DGE)exercises for strength, balance and flexibility on two days per week; aerobic training (3–5 days per week for 20–30 min) planned individually with the participantcognitive training with tablet computers, using the cognitive training software “NeuroNation”, three times per weekenhancement of social engagement, planned individually with the participantif necessary, feedback on vascular risk factors (e.g. smoking, medical history) and ways to reduce the respective riskassessment of depressive symptoms and underlying risk factors (e.g. bereavement, grief); if necessary, patients will be encouraged to contact their GP who will provide adequate support and care (e.g. referring participants to groups, psychiatrists, psychotherapists, psychiatric hospitals); written information on addresses and helplines which can be contacted in case of grief and/or depressive symptoms.optimization of medication: see Table 1 for a detailed description.

**Table 1 Tab1:** Components of the *AgeWell.de* intervention program (intervention group A)

Intervention Component	Description
Nutritional counseling	- Based on the guidelines of the *German Nutrition Society* [33] including recommendations e.g. on intake of cereal products, fruit and vegetables, fish, sugar, salt, and of fluid. - Anthropometric measurements (height, weight, BMI)
Physical activity enhancement	- Combined training program including (i) muscle-strengthening activity, (ii) flexibility activity/balance exercise, on 2 days/week, and (iii) aerobic activity (3–5 days a week for 20–30 min). Strength and flexibility/balance training can be conducted at home. Aerobic training will be planned with each participant individually - Participants will receive a pedometer to record the number of steps walked daily
Cognitive training	- Information on cognitive functioning and the impact of cognitive activity/training on cognitive performance and dementia risk; information on strategies to train cognition in everyday life - Cognitive training at home on a regular basis (3 times/week, 15 min per session) with tablet computers (software: NeuroNation; https://www.neuronation.com/)
Optimization of medication	- Collection of baseline information (i) from the GP on participants’ medication, diagnoses, and lab values (creatinine, hemoglobin A1c) and (ii) from the participants on their actual medication - Electronically supported data evaluation to identify potentially inappropriate medication (e.g. anticholinergics, using a list based on Gray and coworkers [13], potentially missing drugs (using START criteria A1 to A8; [34]), contraindicated drug combinations, and contraindications in patients with renal impairment (using databases from the electronic drug information system AiD*Klinik*). Discrepancies in the information on medication collected from the participant and the GP will be identified. - Reports including recommendations on the medication of a participant will be transmitted to the GP. For recommended drugs, this will include information on potentially serious drug-drug interactions and on drug dose adjustment in patients with renal impairment. A procedure is established in case of emergencies, e.g. if an important drug for a serious condition is not administered by the patient. If a patient reports difficulties with drug administration (difficulties swallowing tablets or capsules, tablet splitting, subcutaneous injections, use of inhalers, transdermal patch application, or with the administration of eye drops, nose drops, ear drops, or rectal or vaginal drug administration), specific information is provided to the patient.
Management of vascular risk factors	- Assessment of medication and diagnoses, lab values, health parameters, lifestyle factors, blood pressure and anthropometric measurements (height, weight) - Information on further vascular risk factors (e.g. smoking, medical history) - Feedback on vascular risk, importance of reducing the risk, and possible ways of achieving such a reduction - Nutritional counseling, recommendation of weight loss (if necessary), physical activity enhancement, and optimization of medication as described above
Enhancement of social engagement	- Assessment of level of social activity and risk of social isolation - Information on the importance of an active lifestyle including high social engagement for dementia risk - Enhancement of social engagement will be planned together with each study participant individually
Bereavement, grief and depressive symptoms	- Assessment of depressive symptoms and underlying risk factors (e.g. bereavement, grief) - If necessary, participants will be encouraged to contact their GP and will be provided with adequate support and care (e.g. referring participants to groups, psychiatrists, psychotherapists, psychiatric hospitals). Additionally, participants will receive written information on addresses and helplines which can be contacted in case of grief and/or depressive symptoms. - If applicable, encouragement to use MoodGym – a scientifically developed and evaluated free web-based training program to prevent and reduce depressive symptoms (http://www.moodgym-deutschland.de/).
Motivational tasks across all components	- Personnel continuity regarding the contact person for the participants - Study nurses will be trained in motivational interviewing techniques and participants will be strongly encouraged to contact their contact person, whenever necessary - Birthday/Christmas/holiday cards originally signed by trial authorities/principal investigators - Participants of intervention A will receive a brochure including recommendations (additional tips and suggestions each week for an active lifestyle, e.g. recipes, suggestions for physical activity, and information on healthy ageing) as well as a weekly diary to track their activities in the intervention components.

Participants of intervention group B (basic) will receive *GP treatment as usual* (GPTAU) and *general health advice* (GHA) related to the components of intervention A. We hypothesize that the multi-component intervention program of intervention A will be superior to GPTAU and GHA (intervention B) regarding trial outcomes.

### Outcomes

#### Primary endpoint

In accordance with previous trials [2, 5, 7], we will assess change in cognitive performance as the primary endpoint. Cognitive performance will be assessed with a neuropsychological test battery covering the six cognitive domains for diagnosing mild and/or major neurocognitive disorder according to DSM-5 (attention, executive function, learning/memory, language, perceptual-motor abilities, and social cognition). Composite cognitive *z-*scores based on the results from all single tests will be calculated. Single *z-*scores will be calculated using baseline mean and standard deviations and then, for the composite score, the single *z-*scores will be averaged.

#### Secondary endpoints

An overview of secondary endpoints (mortality, nursing home placement, instrumental activities of daily living/activities of daily living, quality of life, depressive symptoms, social inclusion, motivation for behavior change, cost-effectiveness) is provided in Fig. 1. Corresponding assessments are detailed in Table 2. Furthermore, we will assess readiness for behavior change and explore mediating and moderating factors for the effectiveness of the intervention.

**Table 2 Tab2:** Instruments used in *AgeWell.de*

*Measures of cognitive performance (primary endpoint)*	
Construct	Instrument
*Cognitive performance* ^a^	• Trail Making Test A and B [35] • Word List Memory - CERAD subtest [36–38] • Verbal Fluency Test - Animals - CERAD subtest [37–40] • Constructional Practice – CERAD subtest [37, 38, 41] • Reading the Mind in the Eyes Test - Revised version [42, 43]^b^ • Montreal Cognitive Assessment (MoCA; [44]).
*Instruments to assess secondary endpoints in AgeWell.de*	
Construct	Instrument
*Mortality*	Information obtained from the GP or confidant elected by the participant [self-constructed items^c^]
*Nursing home placement*	Information from the participant or – if the participant is unavailable or dead – from the GP or a contact person elected by the participant
*ADL/IADL*	Barthel Index [45], Amsterdam-IADL scale [46]^a^
*Quality of life*	EQ-5D and visual analogue scale (EQ VAS scale) [47]; WHOQOL-Bref [48], WHOQOL-Old [49]
*Depressive symptoms* ^a^	Geriatric Depression Scale (GDS; [50, 51])
*Social inclusion*	Lubben Social Network Scale (LSNS; [52] in combination with standardized questionnaire on social activity [self-constructed items^c^]
*Cost effectiveness*	Fragebogen zur Inanspruchnahme medizinischer und nicht-medizinischer Versorgungsleistungen im Alter (FIMA)-Questionnaire for Health-Related Resource Use in an Elderly Population [53]; unit costs for monetary valuation of resource use [54]; EQ-5D [47]
*Motivation for behavior change*	Stage assessment in the adoption and maintenance of physical activity and fruit and vegetable consumption [55–57]
*Instruments to assess further information relevant for the AgeWell.de-trial*	
Construct	Instrument
*Sociodemographic information*	Standardized questionnaire (age, sex, educational level/professional life/activity, living situation/marital status, socio-economic status)
*Subjective cognitive decline* ^a^	Standardized questionnaire on subjective cognitive decline [58]
*Self-reported impairments and symptoms*	Standardized questionnaire on self-reported impairment in walking, vision, or hearing [self-constructed items^c^] Standardized questionnaire on self-reported anticholinergic symptoms [self-constructed items^c^]
*Anthropometry, blood pressure*	Measurement of height, weight, blood pressure; calculation of body-mass-index (BMI)
*Nutrition*	Standardized questionnaire on food consumption (food frequency questionnaire/FFQ [59])
*Physical activity I*	Standardized questionnaire on physical activity [self-constructed items^c^]
*Bereavement, grief*	Standardized questionnaire on bereavement [60]
*Medication I*	(i) Information from the attending GP on participants’ medication (“GP-list”) and diagnoses^b^, lab values using GP practice records and (ii) information from participants on their actual medication (“brown-bag review”), adherence, and difficulties with drug administration using standardized questionnaires [self-constructed items^c^]
*additional vascular risks*	Standardized questionnaires on additional vascular risk factors (e.g. smoking, medical history, familial medical history; [self-constructed items^c^])
*Instruments to assess further information in intervention group A*	
Construct	Instrument
*Physical activity II*	Weekly records on conduct of the physical activity intervention component, training, and pedometer results [self-constructed items^c^]
*Cognitive training*	Weekly records on conduct of the cognitive training [self-constructed items^c^]
*Medication II*	Standardized feedback questionnaires on potential changes in a participant’s medication or reasons for not following the recommendations, completed by the attending GP [self-constructed items^c^]
*Social activity*	Weekly records on social activity, in addition to the information collected on social inclusion (see above)
*Motivation and readiness for change*	Standardized questionnaire on motivation and readiness for behavior change [55–57]
*Instruments to conduct the process evaluation*	
Construct	Instrument
*Success rate of recruitment and quality of the study population*	Standardized questionnaires filled out by the GP practice personnel (number of eligible GP patients, number of participants and non-participants, (baseline) characteristics of participants and non-participants, reasons for non-participation) [self-constructed items^c^]
	Standardized telephone interview on reasons for leaving the study with intervention A-participants, if applicable [self-constructed items^c^]
*Quality of the execution of the intervention, burden for GP patients and GPs*	Standardized interviews with all intervention A-participants on adherence to the intervention components and potential burdens [self-constructed items^c^]
	Standardized GP questionnaires on barriers and facilitators for adherence to intervention components in the GPs’ view and on own potential burdens [self-constructed items^c^]

*GP* general practitioner, *ADL* Activities of Daily Living, *IADL* Instrumental Activities of Daily Living

^a^Information should be also used to diagnose DSM-5 Mild and Major Neurocognitive Disorder/dementia

^b^The composite cognitive z-score for the primary endpoint change in cognitive performance will be calculated based on the test results regarding these six domains

^c^Questionnaires can be obtained from the corresponding author upon request

### Sample size

Sample size calculations are based on a composite *z-*score of cognitive performance from previous findings in mild AD [61], i.e., a mean decrease in the composite *z-*score of cognitive performance of − 0.21 with a common SD of 0.5 is assumed in intervention group B during the two year follow-up period. Accordingly, the required sample size is estimated to be 475 participants per group in order to detect a 50% difference in change in the composite *z*-score between intervention groups (2-sided *t*-test for equal variances; with 5% significance level and 90% power). We assume an inflation factor of 1.1 (corresponding to an intra-cluster correlation coefficient of 0.02 and a cluster size of 6). In view of the findings from the FINGER trial, we further assume a dropout rate of no higher than 10% [5]. Therefore, a total sample size of *n* = 1,152 individuals (*n* = 576 per group) seems sufficient.

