### Recruitment procedure

To ensure the inclusion of 1,152 patients, recruitment will take place at five study sites across Germany (Greifswald, Kiel, Leipzig, and Munich/Halle; Fig. 3). We estimate that (i) 30% of the GP patients between 60 and 77 years are eligible for the study (according to the FINGER trial, approximately 40% have the required CAIDE Dementia Risk Score ≥ 9 [30]; among these another 25% are estimated to be excluded according to the *AgeWell.de* exclusion criteria.). Based on previous experiences from other multi-centric trials [62, 63] and regarding the demanding nature of this prevention trial, we assume a rather conservative response rate of approximately 33%. Thus, every study site will screen *n* = 2,880 GP patients to identify *n* = 864 potentially eligible GP patients (except for Munich/Halle: half numbers due to shared recruitment between the two study sites). To ensure these numbers, we suggest a number of *n* = 24 GP practices per study site (*n* = 96 GP practices in total) as sufficient, leading to a total number of *n* = 12 patients that have to be recruited per GP practice. GP practices will receive monetary incentives for recruitment and provision of patients’ data.

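### The sample size allows for clustering with 6 patients per practice, but the plan recruits 12; at its own ICC and 10% dropout, power is about 86–87%, not 90%

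*Protocol article*

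**What the plan says.** The Sample size section of the protocol article assumes a mean decline of "0.21 with a common SD of 0.5 is assumed in intervention group B during the two year follow-up period". The calculation is made "in order to detect a 50% difference in change in the composite" z-score between the groups, with a "2-sided *t*-test for equal variances", "with 5% significance level and 90% power". This gives 475 participants per group. The figure is then multiplied by 1.1 for clustering, "corresponding to an intra-cluster correlation coefficient of 0.02 and a cluster size of 6". On attrition the section says "we further assume a dropout rate of no higher than 10" per cent. It ends at 576 per group, 1,152 in total.

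The Recruitment procedure section plans 24 practices per study site, with Munich and Halle sharing one allocation: "96 GP practices in total", with "12 patients that have to be recruited per GP practice". The Randomization section names the practice as the cluster and assigns each practice to intervention A or to intervention B.

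**The concern.** The design effect is the only allowance for clustering in the sample-size calculation of this cluster-randomized trial. It is built on half the number of patients per practice that the recruitment plan calls for. Both figures are stated outright in adjacent sections, and they cannot both describe the same design: 1,152 patients in clusters of 6 would need 192 practices, twice the number planned.

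At stake is the power claim. If the cluster size is 12, the trial has less than 90% power for the difference it names, and a null result would be read against a power that the design does not have.

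**Working it through.** **Inputs, all from the protocol article.** Sample size section: difference 0.5 × 0.21 = 0.105, SD 0.5, two-sided 5%, ICC 0.02, dropout at most 10%, 576 per group. Recruitment procedure section: 96 practices, 12 patients each.

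**1. Is the cluster size really 12?**
- 96 × 12 = 1,152, exactly the total in the Sample size section.
- The recruitment figures agree: 2,880 screened × 30% = 864 eligible; about one third respond, giving 288 per site; 288 / 24 practices = 12; 4 × 288 = 1,152.
- Dropout of 10% takes 12 only to 12 × 0.9 = 10.8, so it does not explain 6.
- Six per arm within a practice is ruled out, because each practice belongs to one arm.

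**2. Reproduce the plan's own figures.**
- n per group = 2 × (1.960 + 1.282)² × (0.5 / 0.105)² = 477 (478 with the t distribution), against 475 stated.
- Design effect = 1 + (m − 1) × ICC = 1 + 5 × 0.02 = 1.10, as stated.
- 475 × 1.1 = 522.5. Dividing by 0.9 gives 581; multiplying by 1.1 gives 575. The stated 576 lies close to the second.
- Power check: 576 × 0.9 = 518.4 analysed per group; 518.4 / 1.10 = 471.3 effective; power = Φ(0.105 / (0.5 × √(2 / 471.3)) − 1.960) = 89.7%.

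The stated 90% is thus reproduced with clusters of 6, so the method matches the plan's.

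**3. Repeat with the planned cluster size, same ICC, same 1,152 patients.**

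| Setting | Design effect | Effective n per group | Power |
|---|---|---|---|
| 6 per practice, 10% dropout (as stated) | 1.10 | 471.3 | 89.7% |
| 12 per practice, 10% dropout | 1.22 | 424.9 | 86.5% |
| 10.8 analysed per practice, 10% dropout | 1.196 | 433.4 | 87.1% |
| 12 per practice, no dropout | 1.22 | 472.1 | 89.7% |

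With 94 degrees of freedom (96 practices − 2) instead of the normal approximation, the first three rows become 89.1%, 85.8% and 86.4%.

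**4. What 1,152 patients can detect with 90% power at 10% dropout.**
Difference = (1.960 + 1.282) × 0.5 × √(2 / effective n). This gives 0.111 with an effective n of 424.9 and 0.110 with 433.4.

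**5. What 90% power for 0.105 would need.**
- Design effect 1.22: 475 × 1.22 / 0.9 = 644 per group (1,288 in total), about 54 practices of 12 per arm.
- Design effect 1.196: 475 × 1.196 / 0.9 = 632 per group (1,264 in total), about 53 practices per arm.
- The plan has 96 / 2 = 48 practices per arm.

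**The case against.** The best defence is that the discrepancy is small and that the lower figures count against the plan twice. Taking 10% of patients out of the sample while keeping 12 per practice in the design effect is slightly pessimistic; shrinking the clusters as well gives 87.1%. Dropout is stated as an upper limit, and with none at all the planned design has 89.7%. The degrees-of-freedom correction lowers the clusters-of-6 figure too, so the gap stays at about 3 points. All of this stands. It sets the size of the error at 3 to 4 points. It does not remove the contradiction, because no section explains the 6, and with the plan's own dropout allowance every variant falls below 90%.

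One could also keep the factor 1.1 by supposing a smaller ICC: with 12 per practice it would have to be 0.1 / 11 = 0.009. The section states 0.02, so that reading has no support.

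The dropout step might be read as a second error. The article does not say how dropout was applied; multiplication by 1.1 is only inferred from the result, and the difference is 581 against 576, or 5 patients per group. It is a side correction.

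**Conclusion.** The point holds and is of moderate weight. The stated inflation factor belongs to a cluster size that the design does not have. At the plan's own ICC, effect, SD and maximum dropout, 1,152 patients in 96 practices give about 86–87% power, so the type II error risk is about 13–14% rather than 10%. This assumes practices of equal size. The article gives no variation in practice size, so no figure for unequal clusters is offered.

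Three stronger readings are not supported:
- That the trial is seriously underpowered. A loss of 3 to 4 points is not that.
- That the assumed decline, which the section says comes from mild Alzheimer's disease, makes the shortfall much larger. Whether that decline suits participants without dementia is a separate question. It is unrelated to cluster size, and the article gives no alternative value from which to compute power.
- In the other direction, that adjusting for baseline would win the loss back. That depends on the correlation between baseline and follow-up scores, which the article does not report.

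**What to change.** In the Sample size section, replace the cluster size of 6 and inflation factor of 1.1 with a cluster size of 12 and a factor of 1.22. The existing chain of multiplications then no longer leads to 576, so state the result as power at the planned size. For example: with 96 practices of 12 patients (1,152 in total), an ICC of 0.02 and 10% dropout, power is about 86–87% for a difference of 0.105 z-units, and 90% for a difference of about 0.11. Where dropout is allowed for, divide by 0.9.

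This costs a rewording and a slightly less favourable power statement; recruitment, conduct and analysis are unchanged. If the sponsor wishes to keep 90% power for 0.105, the price is about 632–644 patients per group, or some 5 to 6 more practices of 12 per arm.
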